**FIGURE 2 F2:**
[figure not shown]
Study design. NC, ‘NeedCraft’; NN, ‘NeedNurture.’

### Effect evaluation

2.8

Pre- and post-test data will be collected from all groups to evaluate the effectiveness of the interventions and to evaluate the data over time. This will help ensure accurate quantitative measurement and enable better-informed conclusions and recommendations for the success and sustainability of the intervention (Briñol et al., 2020).

#### Outcome measures

2.8.1

Evaluating the effectiveness of the intervention (i.e., proximal outcomes) will help to determine its success and whether the desired results have been attained. Proximal benefits refer to shorter-term, more immediate, subjective benefits experienced or observed, often as a direct cause of the intervention (i.e., differences in need crafting behavior and perceived managerial support). By contrast, distal outcomes are usually only noticeable over a more extended period of time and often more indirectly as a result of proximal benefits (i.e., changes in need satisfaction).

On the day of training, but before the need crafting workshop starts, participants will need to complete an outcome measure to determine their degree of need crafting, current need satisfaction, and perceived need-support from their immediate managers. The three measuring instruments to be used for the effect evaluation are discussed below (De Angelis et al., 2020). These instruments were selected for their direct alignment with the constructs in the intervention’s program theory and their operationalization, as well as for their explicit grounding in SDT. The adapted NCS operationalizes the proximal outcome targeted by NC (need crafting) and has been validated in the South African work context (Putter et al., 2024). The TMIB-S operationalizes the proximal outcome targeted by NN (perceived need-supportive managerial behaviors) and was developed and validated from an SDT perspective (Huyghebaert-Zouaghi et al., 2023). The single-item need satisfaction scales capture the distal outcome (basic psychological need satisfaction) while minimizing respondent burden across repeated measurement waves, with validity and reliability comparable to multi-item scales (Martela and Ryan, 2026).

The first instrument will be an adapted version of the Need Crafting Scale (NCS) (Laporte et al., 2021), comprising nine items. The original scale was adapted by Putter et al. (2024) to better suit the work context by making small changes to the instructions as well as the wording of items (i.e., references to “in their lives” were changed to “at work,” and “people” were replaced with “colleagues”). Only the three action-oriented items of each subscale will be administered, while the negatively phrased items will be omitted. Previous research found no significant value added from the negatively phrased items, as these items did not load significantly onto their *a priori* factors when controlling for the method factor (Putter et al., 2024). These nine items will be rated on a five-point Likert scale, ranging from 1 (completely not true/disagree) to 5 (completely true/agree). Examples of the items include “*I deliberately choose activities I am good at*” (competence crafting action), “*As much as possible, I try to do things that I really want to do rather than things that have to be done*” (autonomy crafting action), and “*Even when I feel lonely, I still try to contact colleagues who care for me*” (relatedness crafting action).

The second instrument will be the Tripartite Measure of Interpersonal Behaviors-Supervisor (TMIB-S), comprising 22 items, which will measure need-oriented leader behaviors (Huyghebaert-Zouaghi et al., 2023). However, only the “need-supportive behaviors” subscale that comprises eight items will be used to determine the degree to which managers are perceived as supportive following the intervention. Examples of items include “*My supervisor shows that they understand my perspective*” (autonomy support), “*My supervisor recognizes my efforts and accomplishments*” (competence support), and “*My supervisor shows care and concern*” (relatedness support). The need-supportive behaviors subscale will be answered through a seven-point Likert scale, ranging from 1 (strongly disagree) to 7 (strongly agree) (Huyghebaert-Zouaghi et al., 2023). These three instruments will be administered at T2 to T4 (Groups 1 and 2) and T4 to T6 (Group 3).

The last instrument will be the Single-Item Scales for Basic Psychological Need Satisfaction, comprising three items (Martela and Ryan, 2026). These items are “*I am able to do things that I really want and value at work*” (autonomy), “*I can do things well and achieve my goals*” (competence), and “*I feel close and connected with other colleagues who are important to me*” (relatedness). This three-item scale was found to be valid and reliable with strong comparability to multi-item scales. Items will be measured on a seven-point Likert scale, ranging from 1 (very strongly disagree) to 7 (very strongly agree) (Martela and Ryan, 2026).

These same three instruments, as discussed above, will be administered during the 2-weeks reflection meeting held with participants as well as 1 month after the intervention training. These outcome measures will form part of the post-test and will be administered separately to all three groups at different times (first to Group 1 and 2 and then to Group 3) in order to determine the potential changes within each group as well as measure any possible differences between the groups. Each group will undergo two separate post-tests, with all post-testing occurring between T3 and T6 (see Figures 1, 2).

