### Study design

2.1

The current intervention protocol recommends a quasi-experimental mixed-methods design using a partially randomized delayed-start approach with three experimental groups. Departments (clusters) will be randomized to Group 1 (NC + NN) or Group 3 (delayed NC + NN); departments whose managers do not volunteer will form Group 2 (NC only, non-randomized). Group 2 will demonstrate the superiority of a multilevel intervention (i.e., its cumulative effects), whereas Group 3 will serve as a control group until its members have received the intervention.

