Employees will also be asked to identify the department in which they work. The researcher will then randomly assign a number to each department. Similarly, managers will be asked which department they manage, allowing the researcher to allocate the corresponding number to each manager (e.g., accounting department = 1, training department = 2, etc.). Consequently, no names will be required to match departments with managers, and all participants will be reassured of anonymity and confidentiality, since no identifying information will be collected. This will enable employee participants to engage in the need-crafting intervention while also allowing the respective managers to engage in the need-support intervention simultaneously.

During the in-person training sessions, all participants will be asked to complete hard copies of the provided questionnaires using their unique IDs. Subsequent follow-up measures for Groups 1 and 2 (T4) and Group 3 (T6) (Figure 1) will be distributed electronically by the researcher.

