### Data collection and timeline

2.7

As depicted in Figure 2, all three groups will undergo the same pre-testing simultaneously (before any intervention training commences), and it will comprise the following stages: allocate departments to three groups; perform the pre-test data collection on all three groups at the same time and under the same conditions (T1); provide the first two experimental groups with the intervention supplemented by process and outcome measurements (T2); and provide the delayed experimental group with another baseline measurement of the same pre-test assessment battery to account for any possible changes that may have occurred in the time after they were part of the initial pre-test data collection (T3), as well as commence with post-testing on the first two groups (T3). Thereafter, the third group will receive the intervention (T4), followed by post-testing on all three groups 2 weeks after the training and 1 month after they have completed their intervention training to determine the potential impact on the dependent variable (need satisfaction) within each group as well as measure the possible differences between the groups due to delayed intervention delivery. Each group will undergo two separate post-tests, with all post-testing occurring at four different time points (Demerouti et al., 2021; Laporte et al., 2021).

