##### Before the intervention

2.9.1.1

As part of the onboarding process – to prepare employee and managerial participants for the intervention and determine their readiness for such a study – the first process measurement will be administered. This process measurement will capture elements central to participants’ buy-in (i.e., participants’ readiness for change and communication). These and subsequent process measures will be drawn from the Intervention and Multiphase Training Transfer Assessment Questionnaire (IMTTAQ; Vasquez et al., 2026), a validated instrument that assesses contextual factors, transfer mechanisms, and behavioral outcomes across the pre-training, during-training, and post-training integration phases of occupational health training interventions. Examples of the items are “*I am ready to accept the changes brought about by the intervention*” [readiness for change; four items, adapted from Randall et al. (2009)] and “*I have received information about the goals of the intervention*” (communication; three items). These will be measured on a five-point Likert scale, ranging from 1 (strongly disagree) to 5 (strongly agree).

It will, furthermore, also be important to determine participants’ degree of job resources (i.e., autonomy) and job demands (i.e., workload). Example items are “*I am given a lot of freedom to decide how to do my own work*” and “*I never seem to have enough time to get everything done in my job*” [NIOSH Worker Well-Being Questionnaire (WellBQ)] (Chari et al., 2024). These two items will be measured on a four-point Likert scale, ranging from 1 (strongly disagree) to 4 (strongly agree). These two, as well as the above seven items, will be collected at T1 (Groups 1, 2, and 3) and again at T3 (Group 3) (see Figure 1).

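### Sections 2.7, 2.8.1 and 2.9.1.1 disagree on whether outcomes are measured at T1 and T3; under the explicit schedule the randomized comparison shrinks to one unadjusted contrast at T4

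*Protocol article*

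**What the plan says.** Section 2.1 randomizes departments to Group 1 (immediate) or Group 3 (delayed) and states that "Group 3 will serve as a control group until its members have received the intervention". Group 2 is not randomized. Section 2.7 fixes when the control period ends: "Thereafter, the third group will receive the intervention (T4".

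Three passages bear on what is measured before then:

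- Section 2.7 plans to "perform the pre-test data collection on all three groups at the same time and under the same conditions (T1" and, at T3, to "provide the delayed experimental group with another baseline measurement of the same pre-test assessment battery". The stated purpose of the T3 repeat is to allow for change since T1. Neither sentence names the instruments.
- Section 2.8.1, which describes the need crafting, leader-support and need-satisfaction instruments, says "These three instruments will be administered at T2 to T4 (Groups 1 and 2) and T4 to T6 (Group 3". It places the first administration thus: "On the day of training, but before the need crafting workshop starts, participants will need to complete an outcome measure".
- Section 2.9.1.1 says of nine process items (readiness for change, communication, autonomy, workload) that they "will be collected at T1 (Groups 1, 2, and 3) and again at T3 (Group 3".

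Section 2.3 refers to "Subsequent follow-up measures for Groups 1 and 2 (T4) and Group 3 (T6" as sent electronically, so T4 is also the 1-month wave of Groups 1 and 2.

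**The concern.** Only Group 1 versus Group 3 is protected by randomization. Section 3.1 concedes that Group 2 is self-selected through its managers and that comparisons with it may be confounded. An untreated, randomized, concurrent comparator is what would separate an intervention effect from retest effects and calendar change, and the delayed group is there to supply it.

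Section 2.7 reads as if that comparator will be measured at T1 and T3. The schedule in section 2.8.1 has the outcome instruments at neither point for Group 3, and at T1 for no group. If the study team works from section 2.8.1, those scores will not be collected, and no analysis can recover them later. The same conflict leaves it open whether the baseline in Hypotheses 1a, 2a and 3a is T1 or the pre-workshop score at T2.

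**Working it through.** **Schedule laid out by wave.** Inputs are sections 2.3, 2.7, 2.8.1 and 2.9.1.1.

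| Wave | Event | Outcomes, Groups 1 and 2 (2.8.1) | Outcomes, Group 3 (2.8.1) | Stated elsewhere |
|---|---|---|---|---|
| T1 | Pre-test, all groups | none | none | 2.7: pre-test, contents not named; 2.9.1.1: nine process items, all groups |
| T2 | Training, Groups 1 and 2 | yes, before workshop | none | |
| T3 | 2-week post-test, Groups 1 and 2 | yes | none | 2.7: repeat battery in Group 3, contents not named; 2.9.1.1: nine process items, Group 3 |
| T4 | 1-month post-test, Groups 1 and 2; training, Group 3 | yes | yes, before workshop | |
| T5 | 2-week post-test, Group 3 | none | yes | |
| T6 | 1-month post-test, Group 3 | none | yes | |

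Under section 2.8.1 the outcome waves are {T2, T3, T4} for Groups 1 and 2 and {T4, T5, T6} for Group 3. The only shared wave is T4. Group 3 is still untrained when it answers at T4, so it has exactly one control-condition score. Against Group 1's two post-tests:

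- 2 weeks (T3): no Group 3 score.
- 1 month (T4): one Group 3 score, with no earlier Group 3 score to adjust for or to compute change from.

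**What the missing baseline costs at T4.** The documents give no figure for this, so it is an illustration built on the sample sizes in section 2.4. Reproducing those first with an independent-samples t-test at alpha 0.05 and 80% power:

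- d = 0.80: 26 per group two-sided (21 one-sided). The stated 26 agrees with the two-sided result.
- d = 0.50: 64 per group two-sided, 51 one-sided. The stated 51 agrees only with the one-sided result.

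That mismatch is a separate matter and does not affect this point. Two-sided tests are used below.

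Adjusting for a baseline that correlates r with the outcome multiplies the residual variance by 1 − r², so the effective standardized difference is d / √(1 − r²). The value of r is assumed. Clustering is ignored.

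| n per group, d | Post-only | r = 0.3 | r = 0.5 | r = 0.7 |
|---|---|---|---|---|
| 51, 0.50: effective d | 0.50 | 0.52 | 0.58 | 0.70 |
| 51, 0.50: power | 0.71 | 0.75 | 0.82 | 0.94 |
| 26, 0.80: effective d | 0.80 | 0.84 | 0.92 | 1.12 |
| 26, 0.80: power | 0.81 | 0.84 | 0.90 | 0.98 |

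**Cost of closing the gap.** The three instruments have 9 + 8 + 3 = 20 items. Adding them at T1 for everyone and at T3 for Group 3 means 20 more items for each participant in Groups 1 and 2, and 2 × 20 = 40 more in Group 3. The schedule in section 2.8.1 already asks 3 × 20 = 60 of each participant.

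**The case against.** The best defence is that section 2.7 already provides the missing data: a T1 pre-test in all groups and a T3 repeat in Group 3. Its battery is not itemized and may well include the outcomes. Section 2.8 also opens by saying that pre- and post-test data come from all groups to evaluate effectiveness. The sentence with the T2 to T4 and T4 to T6 schedule looks misplaced, since it refers to three instruments when only two have been described. Figures 1 and 2 are not shown and may settle the matter. All of this stands, and it makes the point a contradiction to reconcile rather than a proven omission. It does not remove the contradiction, because the text gives one explicit outcome schedule and that schedule leaves these waves out.

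A reader might infer more: that the control group has no outcome data at all while it is the control, or that the trial cannot estimate an effect against an untreated randomized comparator. The documents do not support this. Group 3's T4 score precedes its workshop and falls in the same wave as Group 1's 1-month score, so a randomized post-only comparison remains possible.

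A reader might also infer that the mixed model will line the groups up on their own pre/post clocks and so compare trained with trained. Section 2.8.2 does not say how time is coded for Group 3, so this cannot be held against the plan.

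Finally, Hypotheses 1 to 3 compare only Groups 1 and 2, and no stated hypothesis uses Group 3. That is true, but section 2.1 still assigns Group 3 the control role, and section 2.7 still intends comparisons that involve the delayed group.

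**Conclusion.** The point holds as an internal contradiction with a material consequence. Sections 2.7, 2.8.1 and 2.9.1.1 do not agree on whether outcomes are measured at T1 and T3. If section 2.8.1 governs, the randomized comparison is one unadjusted contrast at T4: no Group 3 baseline, no concurrent control for the 2-week result, and no measure of change over the control period. If section 2.7 governs and its battery includes the outcomes, the data exist and only the wording needs correcting.

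The power loss at T4 depends on the assumed correlation: at n = 51 and d = 0.50, 0.71 falls short of the adjusted value by 0.04 at r = 0.3 and by 0.23 at r = 0.7. All these powers are optimistic because clustering by department is ignored. The loss of the 2-week randomized contrast depends on no assumption beyond following section 2.8.1. The T4 contrast assumes that waves with the same label fall at the same calendar time in all groups. This should be settled before data collection starts.

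**What to change.** Replace the schedule sentence in section 2.8.1 with an instrument-by-wave-by-group statement, and bring sections 2.7 and 2.9.1.1 and the figures into line with it. The three outcome instruments should be completed:

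- by all groups at T1;
- by Groups 1 and 2 at T2 (before the workshop), T3 and T4;
- by Group 3 at T3, T4 (before its workshop), T5 and T6.

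In section 2.8.2, state that the Group 1 versus Group 3 contrast compares the groups at the same calendar wave, at T3 and at T4 before Group 3's workshop, adjusted for the T1 score. State also which score, T1 or T2, is the baseline for the hypotheses on Groups 1 and 2.

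Keep the group-by-time terms in the mixed model. A single trained yes/no indicator would merge the dual-level with the employee-only intervention, and the 2-week with the 1-month effect, so on its own it could not test the Group 1 versus Group 2 hypotheses.

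The cost is protocol wording plus 20 items at T1 for everyone and 20 at T3 for Group 3. Both waves are already planned, so the added respondent burden is small.

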Step 4: active experimentation (doing)	∙ Participants develop personalized need crafting plans (using the SMART framework to ensure strategies that are specific, measurable, achievable, realistic, and time bound). ∙ Participants brainstorm on enablers and barriers to applying need crafting strategies. They discuss how to optimize enabling factors and mitigate barriers (i.e., inoculation against setbacks). ∙ Participants implement these strategies in their daily work over a set period (i.e., 2 weeks). ∙ After the implementation period, participants reconvene to share experiences, reflecting on the effectiveness of their need crafting efforts and how they can sustain this in the organization.	∙ Participants translate selected activities into SMART goals in their personal need crafting plan, e.g., “walk and talk with a colleague during lunch twice this week” (relatedness); “discuss changes to my schedule with my manager” (autonomy); “offer more input during meetings” (competence, autonomy); “start meetings by asking how everyone is doing” (relatedness).

Adapted from Demerouti et al. (2021).

**TABLE 2 T2:** Overview of ‘NeedNurture.’

Steps	Aspects of support that reflect Kolb’s experiential learning theory	Example activities (targeted needs)
Step 1: concrete experience (feeling)	∙ Participants identify and reflect on their current need-supportive “communication” at work. ∙ They engage in exercises to recognize moments when their actions positively or negatively affect employees’ needs.	∙ Managers recall recent interactions in which their words or actions visibly affected an employee’s motivation, e.g., how they responded when an employee shared an idea, concern, or mistake.
Step 2: reflective observation (watching)	∙ There is guided reflection on these behaviors, analyzing what contributes to need satisfaction or frustration. ∙ Participants discuss how their management practices influence psychological needs.	∙ Managers reflect on critical incidents from their own practice, e.g., keeping reactions to employees’ contributions affirming and uplifting rather than belittling (relatedness and competence support).

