Step 3: abstract conceptualization (thinking)	∙ Managers are introduced to SDT to explain the role of autonomy, competence, and relatedness in fostering employee motivation. ∙ Managers are taught specific strategies to become more need supportive (e.g., offering meaningful choices to employees, providing constructive feedback, and fostering a sense of belonging in the team).	∙ Managers work through strategy examples linked to each need: giving employees input and say in schedules, deadlines, and meeting arrangements (autonomy support); offering coaching or mentoring and competence-affirming feedback (competence support); engaging in appreciative dialogue and regular one-on-one check-ins (relatedness support).
Step 4: active experimentation (doing)	∙ Managers create personalized strategies (using the SMART framework to ensure strategies that are specific, measurable, achievable, realistic, and time bound). ∙ Participants brainstorm on enablers and barriers to applying need-support strategies. They discuss how to optimize enabling factors and mitigate barriers (i.e., inoculation against setbacks). ∙ Managers implement these strategies in their daily work over a set period (e.g., 2 weeks). ∙ After the implementation period, participants reconvene to share experiences, reflecting on the effectiveness of their need-supportive efforts and how they can sustain this in the organization.	∙ Managers translate selected strategies into SMART goals in their personalized need-support plan, e.g., “involve employees in the setting of deadlines and targets” (autonomy support); “help an employee brainstorm a new way to approach a problem” (competence support); “start meetings by asking how employees are doing” (relatedness support).

Adapted from Demerouti et al. (2021).

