#### ‘NeedCraft’ and ‘NeedNurture’

2.6.1

The current study involves two interventions designed to enhance need satisfaction in the workplace. NC is designed to teach employees how to craft their work experiences to better meet their psychological needs. In parallel, NN targets managers, aiming to upskill them to support their subordinates’ basic psychological needs. This standardized protocol will guide the design, effective implementation, and evaluation of the interventions and will also aid stakeholders and managers in future action orientation through more effective decision-making about employee well-being, policy design, etc., (De Angelis et al., 2020).

Both interventions are grounded in Kolb’s learning theory (Kolb, 1984), which holds that effective learning occurs through four stages (see Tables 1, 2). First, learners engage in concrete experiences, followed by reflection on these experiences in the second stage. In the third stage, learners develop abstract ideas about new behaviors and acknowledge their potential benefits. Finally, they actively test these new behaviors, creating new experiences (Demerouti et al., 2021; Kolb et al., 2001; Nielsen and Randall, 2013). NC and NN incorporate these four stages into their learning processes to ensure comprehensive skill development and behavioral change.

The training will be delivered in person, as research shows that face-to-face training tends to yield higher participant satisfaction compared to online formats (Laporte et al., 2024). The program structure consists of an initial 2.5-h training session (see Steps 1–3 in Tables 1, 2), followed by 2 weeks to implement newly acquired skills and behaviors in the workplace. After this implementation phase, a 2-h reflection meeting will be held (see Step 4 in Tables 1, 2) to discuss experiences, reinforce learning, and adjust strategies as needed.

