#### Effect evaluation data analysis plan

2.8.2

Background characteristics will be presented by means of descriptive statistics. Demographic characteristics (i.e., participants’ educational level, age, gender, ethnicity, organization and job tenure, duration reporting to manager, and department) will be used to determine the representativeness of the study sample and potentially to control for their impact on the effects (Bernerth and Aguinis, 2016).

We articulated the following directional hypotheses (H1 to H3) to evaluate the effectiveness of the intervention:

Hypothesis 1a (within-group): both Group 1 (dual-level) and Group 2 (employee-only) will show significant increases in need crafting behaviors from baseline to the 2-weeks and 1-month post-intervention follow-ups.

Hypothesis 1b (between-group): Group 1 will show significantly greater increases in need crafting behaviors compared to Group 2 at the 2-weeks and 1-month follow-ups.

Hypothesis 1c (sustainability): Group 1 will maintain higher levels of need crafting from the 2-weeks to the 1-month follow-up, while Group 2 may show some decline.

Hypothesis 2a (within-group): Group 1 will show significant increases in perceived need-supportive leadership behaviors from baseline to the 2-weeks and 1-month follow-ups, while Group 2 will show minimal or no change.

Hypothesis 2b (between-group): Group 1 will show significantly higher perceived need-supportive leadership behaviors compared to Group 2 at the 2-weeks and 1-month follow-ups.

Hypothesis 2c (sustainability): Group 1 will maintain elevated levels of perceived need-supportive leadership from the 2-weeks to the 1-month follow-up, while Group 2 will remain stable at baseline levels.

Hypothesis 3a (within-group): both groups will show increases in need satisfaction from baseline to the 2-weeks and 1-month follow-ups.

Hypothesis 3b (between-group): Group 1 will show significantly greater improvements in need satisfaction compared to Group 2 at the 2-weeks and 1-month follow-ups.

Hypothesis 3c (sustainability): Group 1 will maintain or further improve need satisfaction from the 2-weeks to the 1-month follow-up, while Group 2 effects may diminish over time.

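### The first post-test is taken at a reinforcing programme session, so the change from 2 weeks to 1 month read by H1c, H2c and H3c is not maintenance without further intervention

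*Protocol article*

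**What the plan says.** Section 2.6.1 sets out two delivered components. "The program structure consists of an initial 2.5-h training session", covering Steps 1 to 3, and participants then practise for 2 weeks. "After this implementation phase, a 2-h reflection meeting will be held", covering Step 4, with the aim "to discuss experiences, reinforce learning, and adjust strategies as needed". In Table 1 (NeedCraft), Step 4 ends when "participants reconvene to share experiences, reflecting on the effectiveness of their need crafting efforts and how they can sustain this in the organization". Table 2 gives managers in NeedNurture the same kind of meeting, "reflecting on the effectiveness of their need-supportive efforts and how they can sustain this in the organization". Section 2.9.1.3 adds a focus group at that meeting which also asks how the actions can be made to last.

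On measurement, section 2.8.1 says the three outcome instruments "will be administered during the 2-weeks reflection meeting held with participants as well as 1 month after the intervention training". Section 2.7 describes the same two post-tests as "2 weeks after the training and 1 month after they have completed their intervention training".

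In section 2.8.2, H1a calls both time points post-intervention. The hypotheses labelled sustainability use the interval between them. H1c, for example, expects that "Group 1 will maintain higher levels of need crafting from the 2-weeks to the 1-month follow-up", while Group 2 may decline. H2c and H3c use the same interval for perceived need support and need satisfaction. All three name only Groups 1 and 2.

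Section 3.1 acknowledges that a horizon of 1 month after training limits conclusions about sustainability. It does not mention that a programme session falls at the start of the interval.

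**The concern.** A sustainability hypothesis asks whether an effect persists once the intervention has stopped. Here the starting measurement is collected at a meeting designed to reinforce the training, revise each person's strategies and discuss how to keep the behaviour going. A stable or rising score from 2 weeks to 1 month could mean that the effect of the first session lasted, or that it faded and the meeting topped it up. The report would describe both as sustained effect.

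The label on the 2-week score has a related problem. If the questionnaire comes before the meeting content, the score reflects the first session plus 2 weeks of practice, not the completed programme. If it comes after, the score already carries any immediate reaction to the meeting. The article does not say which applies.

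**Working it through.** The plan gives no figure to reproduce on this point. The check is a timeline followed by a count of what the measurements can identify.

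**Timeline for Groups 1 and 2** (sections 2.6.1, 2.7 and 2.8.1; Tables 1 and 2)

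| Time from first session | Event |
|---|---|
| Day 0 (T2) | Baseline outcome battery, then 2.5-h session |
| Days 0 to 14 | Practice in the workplace |
| Day 14 (T3) | 2-h reflection meeting, with the first post-test taken during it |
| T4 | Second post-test, at 1 month |

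**Length of the interval.** Take 1 month as 28 to 31 days.

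- Counted from the 2.5-h session: 28 − 14 = 14 days, up to 31 − 14 = 17 days, between the reflection meeting and the final follow-up.
- Counted from the reflection meeting (one possible reading of section 2.7): 28 to 31 days. The final follow-up then falls 14 + 28 = 42 to 14 + 31 = 45 days after the first session.

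Under either origin the interval opens at the reflection meeting.

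**Identification within one group.** Let m be the mean at the first post-test, d the decay that would occur over the interval with no further input, and b the effect of the reflection meeting seen by the final follow-up.

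- Mean at T3 = m
- Mean at T4 = m − d + b
- Change from T3 to T4 = b − d

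There are three unknowns and two means; the design matrix has rank 2. A flat profile (change = 0) fits d = 0 with b = 0, and equally d = b = 0.1, 0.2 or 0.3. The data cannot choose between these.

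**Identification across Groups 1 and 2.** Both groups have the NeedCraft meeting (effect b_NC). Only Group 1 also has the managers' NeedNurture meeting (effect b_NN).

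- Group 1 change = b_NC + b_NN − d1
- Group 2 change = b_NC − d2
- Difference = b_NN + (d2 − d1)

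There are six unknowns (m1, m2, d1, d2, b_NC, b_NN) and four means; the rank is 4. If b_NC is the same in both groups, it drops out of the difference. The difference in decay that H1c and H3c want to show, d2 − d1, still arrives added to b_NN. For H2c the outcome is the direct target of the managers' training, so b_NN matters most there.

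**Order within the meeting.** If the battery is completed at the end of the meeting, no contact time remains inside the interval. Any effect of the meeting on behaviour at work can still appear only afterwards, so b stays in the T3-to-T4 change.

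**The case against.** Several points on the other side are fair.

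- **Section 3.1 already limits sustainability claims**, and section 3.2 proposes follow-up at 6 or 12 months. This stands as a caveat about a short horizon, but it does not tell the reader that a reinforcing session opens the interval.
- **The comparison with Group 2 may protect the hypotheses.** This stands in part for H1c and H3c, where the shared employee meeting may cancel. It does not remove the managers' meeting. A reader might infer that all three hypotheses fail alike; the documents do not support that.
- **The order of questionnaire and meeting is operational detail that an article can omit.** This carries less weight here, because the article fixes the order elsewhere: the baseline battery precedes the workshop (section 2.8.1) and the process survey directly follows training (section 2.9.1.2).
- **The two descriptions of the month can be read together.** A reader might infer a contradiction between section 2.7 and sections 2.8.1 and 2.9.1.4. Section 2.6.1 uses intervention training for the 2.5-h session, so all three may share one origin. The wording is ambiguous, not contradictory.

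Three further inferences are tempting but unsupported. Nothing says that the amount of programme received at T3 varies between participants; only the order is unstated. No sustainability hypothesis covers Group 3. The ratio of 2 h to 4.5 h of contact is not a measure of dose, because the concepts and the personal plan are delivered in the first session and the 2 weeks of practice count for nothing in that ratio.

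**Conclusion.** The point holds. A programme session intended to reinforce and sustain the behaviour opens the interval that H1c, H2c and H3c read as sustainability, and the score at the start of that interval is called post-intervention although it is collected during the session. Within-group maintenance is not identified in either group. The consequence is greatest for H2c and smaller for the Group 1 versus Group 2 contrasts of H1c and H3c, provided the NeedCraft meeting has the same effect in both groups. Three of the nine stated hypotheses (1a to 3c) rest on this interval.

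The conclusion depends on reading the reflection meeting as intervention, which its place in the programme structure and its stated purpose support. The figure of about 2 weeks after last contact assumes that the month is counted from the 2.5-h session. The size of any resulting bias cannot be estimated, because the documents give no figure for decay or for the effect of the meeting.

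**What to change.** 1. In section 2.8.1, require the outcome battery at T3 (Groups 1 and 2) and T5 (Group 3) to be completed on arrival, before any reflection-meeting content. Describe the score as the effect of the first session plus 2 weeks of practice.
2. In section 2.8.2, restate H1c, H2c and H3c as change from that point to the final follow-up after the full two-session programme, not as maintenance without further intervention.
3. State one origin for the month in sections 2.7, 2.8.1 and 2.9.1.4.
4. In section 3.1, say that the interval begins at a reinforcing session and that, if the month is counted from the 2.5-h session, about 2 weeks remain after last contact.

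Moving the final follow-up so that it is counted from the reflection meeting would lengthen the interval but leave the session at its start, so it would not justify keeping the sustainability label.

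The cost is a handout instruction and edits to the text; no visit needs to be added or moved. The price is a more modest claim about durability.
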